## **5 RANDOMIZATION**

Once informed consent has been provided, the investigator should obtain the result of the randomization. Based on the random number table without stratification or blocks, patients will be assigned to one of the two intervention groups (1:1 ratio): iTBS stimulation-first or sham stimulation-first group.

## 6 STUDY POPULATION

### 6.1 Eligibility criteria

#### Inclusion Criteria:

- VS/UWS or MCS according to at least two CRS-R assessments
- Age  $\geq 18$  years
- Time since brain injury between 15 days and 1 year
- Written informed consent obtained from the legal surrogate

#### Exclusion Criteria:

- Brain injury due to unknown etiology
- History of mental or psychiatric disorder prior to the brain injury
- Uncontrolled seizures or status epilepticus
- Unstable or deteriorating medical condition
- Contraindications to MRI
- Skull defect
- Contraindications to TMS

### 6.2 Recruitment and screening

All patients will be recruited and pre-screened by an experienced neurologist based on the inclusion and exclusion criteria. Caregivers of potential candidates will be informed about the trial, and eligible patients will be transferred to the Coma Awakening Center for a comprehensive baseline assessment and further eligibility verification.

### 6.3 Assignment to study groups

After the baseline assessment and final eligibility check, the study patients will be randomly allocated by an investigator who will not be involved in the treatment, data analysis and follow-up.

## 7 STUDY INTERVENTION

### 7.1 Rest motor threshold determination

Bilateral RMTs are assessed prior to the initial administration of either active or sham stimulation on the same day, using single pulses delivered via an eight-figure coil positioned over the corresponding hemisphere of the patient's right and left hands, respectively. This is indicated by a visually detectable twitch in the abductor pollicis brevis muscle. Given the abnormal corticospinal excitability associated with various brain injuries in some patients with DoC, RMT may not be determinable in some patients or on certain sides. For patients with only one side of RMT detectable, the intensity of iTBS is based on this detectable RMT. For patients with both sides of RMT undetectable, 50 % of maximal stimulator output will be used as RMT, as previously

described.

## 7.2 iTBS stimulation

iTBS stimulation will be delivered by targeting the VII lobule of the cerebellum. Structural MRI scans will be performed and uploaded to a neuronavigation system (Quicks Vision, Yingchi, Shenzhen, China) to precisely localize the VII lobe of the cerebellum for each participant based on the MR atlas. During stimulation, the position and orientation of the coil will be localized and maintained through the neuronavigation system. Cerebellar iTBS will be delivered with a double-cone coil in 90 mm diameter connected to the TMS device (M-100 Ultimate, Yingchi, Shenzhen, China). The stimulation intensity will be set at 90% of the RMT of the contralateral primary motor cortex, adjusted according to the individual scalp-to-cortex distance. The iTBS pattern is 3 pulses at 50 Hz repeated at 5 Hz, and a 2 s train of TBS was repeated every 10 s, for a total of 200 s (600 pulses). During each stimulation session, the left and right hemispheres of the cerebellum are sequentially stimulated, separated by 5-min interval. Sham stimulation will be delivered by rotating the coil 90 degrees from the scalp over the targeting position. All patients wear earplugs during stimulation to block out auditory interference.

## 7.3 Sham stimulation

In the sham intervention phase, all participants undergo the same procedure as the active intervention, except that the coil is rotated 90 degrees from the scalp over the target position.

## 7.4 Concomitant treatments

During the study period, all participants will receive routine neurocritical care management. Medications that may have potential influences on cortical excitability, such as sedative drugs, are suspended from baseline assessment until the end of the last EEG and behavior assessments to avoid interference with the evaluation of EEG and consciousness.

# 8 STUDY ASSESSMENTS

## 8.1 Level of consciousness

Two qualified and independent neurologists who are blinded to the patient allocation evaluate the CRS-R scores. The CRS-R is subdivided into six subscales, including auditory, visual, motor, oromotor/verbal, communication, and arousal, for a total of 23 points to assess both the conscious awareness and arousal aspects of DoC patients. Diagnoses of VS/UWS and MCS (minus or plus) are determined based on the presence of specific items during subscale assessments. The baseline consciousness is determined by the highest score obtained from at least two CRS-R assessments during enrollment. The consciousness level during the follow-up phase will be evaluated via

structured telephone interviews developed from CRS-R, either with patients themselves or close relatives.

## **8.2 Definition of consciousness improvement and unimprovement**

According to the 6-month consciousness, patients will be categorized into the improved consciousness group if they transition from UWS to MCS or emergence from MCS (EMCS), from MCS minus to MCS plus or EMCS, and from MCS plus to EMCS. Patients with unimproved consciousness are defined as those with a reduced or unchanged level of consciousness at six months. Patients with unimproved consciousness are defined as those with a reduced or unchanged level of consciousness. If patients die during the follow-up period, their consciousness will be evaluated based on their level of consciousness before death. For patients who die between 3 and 6 months after treatment, their pre-death consciousness will be assessed based on their condition at 3 months post-treatment. For those who die within 3 months of treatment, their pre-death consciousness will be evaluated according to their consciousness at the time of discharge.

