### Structured Telephone Questionnaire based on CRS-R

| Subscale                    | Question |                                                                                                                                                                        |
|-----------------------------|----------|------------------------------------------------------------------------------------------------------------------------------------------------------------------------|
| Auditory             | #        | Has the patient at any point been able to follow instructions (e.g. to fix a certain object or deliberately move a part of the body)?                                  |
|                             | •        | Did you ever detect eye opening or movements of the head in response to direct speech?                                                                                 |
|                             | •        | Did you ever detect an eyelid movement, a blink or any other reaction in response to direct speech?                                                                    |
| Visual               | #/*      | Upon instruction, is the patient able to touch a given object or to move a limb towards this object?                                                                   |
|                             | *        | Is the patient able to fix a given object and to track this object when it is moved?                                                                                   |
|                             | *        | Is the patient able to fix any object or person with her or his eyes (e.g. you)?                                                                                       |
| Motor                | †        | Upon instruction, is the patient able to use common objects (e.g. a comb, a cup or a toothbrush)?                                                                      |
|                             | *        | Did you ever observe any spontaneous or automatic movements by the patient? If so, describe the situation(s).                                                          |
|                             | */•      | Have you ever detected any reaction to pressure, pain or passive movement of the patient's body?                                                                       |

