## 6 EFFICACY ANALYSIS

Continuous variables will be expressed as mean  $\pm$  standard deviation (SD) or median (interquartile range, IQR), and categorical variables will be expressed as percentages. Baseline continuous variables will be analyzed using Student's t-test for normal distribution and Mann - Whitney U test for skewed distribution. Categorical variables will be analyzed using  $\chi^2$  test analysis and Fisher's exact tests, when appropriate.

Besides the primary and secondary outcomes mentioned above, we will conduct a post-hoc analysis of the changes in CRS-R scores and EEG after the first treatment session. At three- and six-months post-treatment, the consciousness of patients will be additionally assessed based-on CRS-R via telephone interview.

The between-group differences in the change of CRS-R total and subscale scores after the first and fifth treatment sessions will be analyzed using a linear mixed model (LMM) with fixed effects (sequence, period, time since injury, etiology, and age) and random effects (subjects for repeated measurements).

The effects of cerebellar iTBS on CRS-R total scores will be further analyzed in subgroups of patients according to their baseline characteristics, i.e., VS/UWS and MCS, as well as anoxia etiology and non-anoxia etiology.

The between-group differences in PSD after the first and fifth treatment sessions will also be analyzed via LMM, incorporating baseline PSD as a fixed effect alongside other fixed and random variables as above.

The cumulative link mixed effects model (CLMM), which incorporated fixed and random effects as those of LMM (fixed effects: sequence, period, time since injury, etiology, and age; random effects: subjects for repeated measurements) and added baseline "ABCD" EEG patterns as fixed effects, will be used to analyze the between-group differences in "ABCD" EEG patterns after the first and fifth treatments.

We will use the ordinal logistic regression to explore the relationships between the baseline "ABCD" EEG patterns and the functional outcomes and recovery of consciousness six months post-treatment. To investigate the relationships between EEG responsiveness and six-month outcomes, we will use the generalized linear model (GLM), with adjustments made for baseline characteristics and time period.

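### A patient who improves and then dies is counted as improved on the six-month consciousness outcome, and half of the telephone items record past rather than current status

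*Supplement*

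**What the plan says.** Protocol V2.0, section 8.2, ties the classification to a fixed time: "According to the 6-month consciousness, patients will be categorized into the improved consciousness group if they transition from UWS to MCS", with further upward steps listed after it. The other group is defined at the same time point: "Patients with unimproved consciousness are defined as those with a reduced or unchanged level of consciousness at six months".

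Deaths follow a separate rule. In general, "If patients die during the follow-up period, their consciousness will be evaluated based on their level of consciousness before death". For death between 3 and 6 months after treatment, "their pre-death consciousness will be assessed based on their condition at 3 months post-treatment". For earlier deaths: "For those who die within 3 months of treatment, their pre-death consciousness will be evaluated according to their consciousness at the time of discharge". Death is neither a category of its own nor assigned to the unimproved group.

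Consciousness at follow-up is obtained with the telephone questionnaire in the protocol appendix. Its first item begins: "Has the patient at any point been able to follow instructions".

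SAP V2.0, section 6, relates baseline ABCD EEG pattern to "functional outcomes and recovery of consciousness six months post-treatment" by ordinal logistic regression, and EEG responsiveness to six-month outcomes by a generalized linear model (GLM). SAP section 5 has one missing-data rule, last observation carried forward, and says nothing specific about death.

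**The concern.** The outcome is presented as status at 6 months, but for some patients it is status at an earlier date. A patient in UWS at enrolment who is in MCS at the 3-month call and dies in month 5 enters the improved group. So does one who reached MCS by discharge and died in month 2. A reader told that a given share had improved consciousness at 6 months would take these patients to be alive and improved.

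The telephone form adds a second gap of the same kind among survivors. Where an item asks whether something was *ever* seen, a behaviour that appeared once and was then lost still earns credit at the call.

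What is at stake is the meaning of the six-month improvement figure and of the two models that use it. With at most 44 patients in those models, a few patients placed differently can matter.

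**Working it through.** The plan states no mortality or improvement rate, so there is no figure of its own to reproduce. The check traces the rule, sizes it under stated assumptions, and counts the telephone items.

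**1. Tracing the rule (protocol 8.2).**

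| Course | Level used | Group |
|---|---|---|
| UWS at baseline, MCS at 3 months, dies in month 5 | 3-month level: MCS | improved |
| UWS at baseline, MCS at discharge, dies in month 2 | discharge level: MCS | improved |
| UWS at baseline, UWS at discharge, dies in month 2 | discharge level: UWS | unimproved |

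For a death between 3 and 6 months, the level used can be up to 6 − 3 = 3 months old. The discharge level has no scheduled CRS-R assessment in the text available (the flow chart is not reproduced there), and no value is given for a patient who dies before discharge.

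**2. Direction.** Let *m* be the proportion dead by 6 months and *q* the proportion of those classed as improved at the level carried forward. With the same denominator,

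proportion improved (present rule) − proportion improved (death as unimproved) = *m* × *q* ≥ 0.

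No patient moves the other way, so the present rule gives a proportion that is equal or higher, never lower.

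**3. Size.** N = 44 comes from the sample-size section. Both *m* and *q* are assumptions, because the documents give neither. Patients affected = 44 × *m* × *q*; percentage points in brackets = 100 × *m* × *q*.

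| *m* | Deaths (44 × *m*) | *q* = 10% | *q* = 30% | *q* = 50% |
|---|---|---|---|---|
| 10% | 4.4 | 0.4 (1) | 1.3 (3) | 2.2 (5) |
| 20% | 8.8 | 0.9 (2) | 2.6 (6) | 4.4 (10) |
| 30% | 13.2 | 1.3 (3) | 4.0 (9) | 6.6 (15) |
| 40% | 17.6 | 1.8 (4) | 5.3 (12) | 8.8 (20) |

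**4. Telephone items (protocol appendix).** There are 12 items.

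- *Ever* or *at any point*: 6 items (three auditory, two motor, one verbal).
- Any time since hospital discharge: 1 item (communication).
- Present tense: 5 items (three visual, the object-use item, arousal).

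Four items carry the MCS+ mark: command following, reaching on instruction, verbalisation and communication. Three of the four (all but reaching) are cumulative. Two items carry the EMCS mark: object use is in the present tense, and communication is cumulative. A patient who followed a command once and then lost the ability can still be recorded as MCS+ at 6 months.

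**5. Reach.** SAP section 2.2 lists CRS-R total change after five sessions as primary; CRS-R subscales, ABCD patterns and PSD after five sessions as secondary; and GOS-E as the follow-up outcome. None of these uses the section 8.2 classification. Section 6 describes six-month consciousness as additionally assessed. It enters only the ordinal regression on baseline EEG pattern, which is stated as exploratory, and the GLM on EEG responsiveness. Neither is an iTBS-sham comparison.

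**The case against.** The strongest reply is that the rule is explicit, set in advance and visible to any reader, with a source named for each interval. The level reached before death is a defensible estimand: a patient who regained awareness and then died of an unrelated cause did regain awareness, and calling that a neurological failure answers a different question. This stands. The defect is that the outcome is labelled by a time point the rule does not respect, and that no alternative analysis is planned. A reader who inferred that the plan forgot about death would be wrong.

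Three other strong readings are tempting, and the documents do not support them.

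- *That the two six-month outcomes contradict each other.* Level of consciousness and GOS-E function are different constructs with different cut-offs. A patient can improve on one and do badly on the other without inconsistency.
- *That the EEG associations are biased in a known direction.* This depends on how deaths after improvement are spread over EEG patterns and responders, and the documents say nothing on that. Only the effect on the proportion improved is one-sided.
- *That decline cannot be recorded by telephone.* The visual, object-use and arousal items ask about the present, so some losses will show. The form mixes current and cumulative status. It is adapted from cited sources whose scoring instructions are not available here.

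It is also fair to say that eligibility excludes unstable or deteriorating patients and requires at least 15 days since injury, which may keep mortality low. The documents put no number on it.

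**Conclusion.** The point holds as one about what the six-month consciousness outcome means. Patients who improve and then die are counted as improved, which can only raise the reported proportion or leave it unchanged relative to counting death as unimproved. Under assumed mortality of 10% to 40% and prior improvement in 10% to 50% of those who die, the difference is 1 to 20 percentage points; the middle case (20% and 30%) is 6 points, or 2.6 of 44 patients. These inputs are illustrative, and the range is too wide to say whether the effect will be trivial or substantial. Half of the telephone items add a further, unquantified route by which a transient gain counts as six-month improvement.

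A reader might infer that the trial's efficacy result is compromised. It is not: the primary CRS-R comparison, the iTBS-sham contrast and GOS-E do not use this classification. The matter is confined to exploratory follow-up analyses. It deserves correction because the remedy is cheap and determines what the six-month result can be said to show.

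**What to change.** In protocol 8.2 and SAP section 6, specify two analyses of the six-month consciousness outcome. One treats death before 6 months as unimproved, or as its own lowest category where an ordinal form is used; the SAP should say which form enters the ordinal regression. The other keeps the present rule, labelled as last level before death. Report the number of deaths and how many of them the present rule classed as improved. In the appendix, word the telephone items so that all ask about current status at the 3- and 6-month calls.

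The cost is an amendment to the wording and a second fit of each model, with no added patients or visits. There are two downsides. Deaths unrelated to brain recovery count as unimproved in one of the two analyses, which the other analysis makes visible. The telephone items also depart slightly from their source wording.

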## **8.3 Functional outcome assessment**

GOS-E is utilized to evaluate the functional outcome 3 and 6 months after treatment, with a score of  $\geq 4$  indicating a favorable outcome and  $< 4$  indicating an unfavorable outcome. It will be conducted by another trained and independent evaluator through structured phone interviews.

## **8.4 EEG recording and analysis**

### **8.4.1 EEG recordings**

EEG signals are recorded using 32 Ag/AgCl ring electrodes connected to an amplifier system (BrainAmp MR Plus, Brain Products GmbH, Gilching, Germany). The electrodes are positioned according to the international 10-20 system. The EEG data acquisition occurs at a sampling rate of 1000 Hz, with impedance kept below 5 k $\Omega$ . EEG data is continuously monitored for 20 minutes, within 30 minutes before and after the first stimulation session, as well as after the fifth stimulation session. Patients are lying on the beds, awake with their eyes open. An arousal-promoting protocol will be implemented if their eyes are closed as previously described.

### **8.4.2 EEG data pre-processing**

Pre-processing and all subsequent analyses are carried out in MATLAB 2023a using the EEGLAB toolbox (<https://sccn.ucsd.edu/eeglab/index.php>). First, the recorded EEG data, with a sample frequency of 5000 Hz, is downsampled to 500 Hz. Next, the data are processed using a notch filter (48-52 Hz) and a band-pass filter (0.5–70 Hz).

Following this, EEG segments with obvious artifacts are manually removed. Then, channels removed due to noise are interpolated with cleaned data, and independent component analysis (ICA) is performed to remove excessive eye movements and movement artifacts. Finally, each channel is re-referenced to the average of all channels.

### **8.4.3 Power spectra density and EEG pattern categorization**

Power spectral density (PSD) and EEG pattern categorization are analyzed to evaluate the neurophysiological efficacy of five consecutive sessions and a single session of iTBS simulation targeting the bilateral cerebellum.

We estimate the power spectrum using Welch's method by segmenting EEG signals into equal-sized 5-second signals. Each 5-second signal is then further segmented into sub-bands with a 50% overlap rate between adjacent sub-bands using a sliding window. Meanwhile, the Fast Fourier Transform (FFT) is applied to the overlapping segments and averaged in the frequency domain to reduce noise.

We generate PSD plots for each trial over the 1 to 70 Hz frequency range. Consistent with previous studies, the data are analyzed in six different frequency bands: delta (1-4 Hz), theta (4-8 Hz), alpha (8-13 Hz), beta (13-30 Hz), low gamma (30-50 Hz), and high gamma (50-70 Hz).

“ABCD” EEG pattern analysis is based on the power spectrum density across different frequency bands, which decodes the integrity of thalamocortical circuitry and the preservation of consciousness. The “ABCD” EEG patterns are defined as follows: (1) Pattern A refers to the complete loss of thalamocortical integrity, and only delta frequency ( $< 4$  Hz) exists; (2) Pattern B refers to a narrow oscillation of layer V pyramidal cells in the theta frequency range (4-7 Hz), which is due to the depolarization of neocortical neurons with depressed membrane potentials; (3) Pattern C refers to an oscillation of theta and beta frequencies resulting from the partial restoration of neocortical membrane potentials and coincident bursts of deafferented thalamic neurons; (4) Pattern D refers to the normal neocortical neuronal firing pattern at alpha and beta frequencies. Two qualified EEG technicians analyze the EEG independently, and disagreement is resolved by consulting a third EEG technician.

### **8.4.4 Definition of EEG responsiveness to cerebellar iTBS**

The EEG responsiveness to cerebellar iTBS is defined as patients who exhibited elevated levels of “ABCD” EEG patterns compared to the baseline after either the first or fifth session of iTBS stimulation.

## **9 DATA MANAGEMENT AND QUALITY ASSURANCE**

### **9.1 Confidentiality**

All data will be handled using Microsoft Excel software. Detailed patient information is available solely for this trial and will not be used for any other purpose.

